### Covariate adjusted analysis of the primary and secondary outcomes

Adjusted analyses will be carried out on the primary and secondary outcomes to determine whether the estimate of treatment-effect is affected by the inclusion of additional covariables. The prespecified covariates will be developed and tested prior to final analysis but specific to each site. For the primary and secondary outcomes, one additional analysis will include all covariables which are used in restricted randomization with variables treated exactly as specified in randomization. Because these variables cannot be fully prespecified until the restricted randomization is complete, the full specification of these covariables cannot yet be made. However, these analyses will be prespecified for the primary outcome prior to data lock and the statistical analysis plan for each trial site will be updated to reflect these analyses. Examples of prespecified covariates that may be included in the adjusted analyses are described in Table 7 which will be finalized prior to data lock.

**Table 7 Tab7:** Proposed covariables

Variable	Categorization (if applicable)	Analysis	Analysis population
Baseline prevalence	Calculated at cluster level	Clinical incidence, prevalence	ITT, per-protocol
Baseline incidence	Calculated at cluster level	Clinical incidence, prevalence	ITT, per-protocol
Rainfall (anomaly)	Summarized monthly at cluster level (lagged one month preceding) as anomaly	Clinical incidence, prevalence	ITT, per-protocol
Season		Clinical incidence, prevalence	ITT, per-protocol
Year	One vs. Two	Clinical incidence, prevalence	ITT, per-protocol
Age	Under 60 months vs. greater than 60 months	Clinical incidence, prevalence	ITT, per-protocol

### Subgroup analysis of the primary outcome

We will perform a series of subgroup analyses according to the list of subgroups in Table 8*.* Imputation for these baseline missing covariates (see the section “Missing data”) will be carried out before categorizing. Assessment of the homogeneity of treatment effect by a subgroup variable will be conducted by the inclusion of the treatment, subgroup variable, and their interaction term as predictors in the adjusted models of primary outcome, and the *p*-value presented for the interaction term. If the *p*-value is less than 0.05, we will present separate effect estimates and confidence intervals for each category of the sub-group variable.

**Table 8 Tab8:** Planned sub-group analyses

Subgroup name	Categorization	Rationale
Housing type	Closed eaves vs. Non-closed eaves	House structure may act as effect modifier by eliminating indoor biting risk independent of ATSB deployment
Gender	Male vs. Female	Behavioral and occupational difference may act as effect modifier; to demonstrate equity of the intervention effect
One month lagged rainfall (total m per m^2^ previous month)	High vs. low (≥ mean for study site (country) vs. < mean for study site (country))	High levels of absolute rainfall may reduce impact of ATSB by increasing environmental carrying capacity for mosquito population
Season	High vs low (four continuous months of the year with the highest clinical malaria incidence at local health facilities during the trial) vs. eight months with lower incidence	(Kenya only)
Age	≤ 60 months of age vs > 60 months of age	Behavioral differences by age may act as effect modifier
Baseline prevalence	High vs. low (≥ median cluster prevalence vs. < median cluster prevalence)	Local endemicity may act as an effect modifier

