#### Secondary outcomes

Prevalence of malaria infection among participants aged 6 months and older, detected by RDT. This outcome will be assessed annually cross-sectionally (or through a rolling prevalence survey in Kenya). For the cross-sectional analyses (Zambia, Mali), measurement will occur in each member of the study sample within an approximate 1-month (30-day) observation window.Incidence rate of passively reported clinical malaria among participants of all ages, defined as the number of malaria confirmed cases (by RDT or microscopy), linked to study clusters by place of residence, per 1000 population per year, using routine data from health facilities serving the study population (e.g., by name of village of residence) and cluster population sizes for the denominator. This outcome is assessed daily at routine health facilities and dispensaries (Mali and Kenya only).Parity as a proxy for daily female vector mosquito survival—this outcome is defined as the non-parous proportion, e.g., the proportion of freshly-caught, non-blood-fed female adult *Anopheles* spp. mosquitoes captured during Human Landing Catches which have never been gravid as determined by the method of Detinova. The outcome is assessed in a sub-sample of clusters, houses, and nights on a monthly basis.Mosquito abundance—The number of adult *Anopheles* spp. captured in CDC UV Light traps.Sporozoite rate—The number of adult female *Anopheles* spp*.* captured via HLC or CDC UV light traps found to be sporozoite positive by anti-circumsporozoite protein (α-CSP) enzyme-linked immune-sorbent assay (ELISA) divided by the number of adult female *Anopheles* spp. tested in ELISA assay.Human landing/biting rate—The number of adult female *Anopheles* spp. captured via HLC divided by the number of person-nights (days) of HLC collection.Entomological inoculation rate—The human landing/biting rate (6) multiplied by the sporozoite rate (5) multiplied by 365 days per year to yield annualized EIR. It should be noted that all EIR estimates will be expressed in terms of annual rates.

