### Eligibility

Eligibility for participation is described in detail in the protocol but in short, the cohort monitoring requires that the individual resides in the study areas within the core sampling areas and additionally is a:Household residentAt least 12 months of age and less than 15 years of age at the time of enrollment (≥ 5 to 15 in Mali, to exclude those covered by Seasonal Malaria Chemoprevention).

And is not a:Resident whose home is located within a buffer zonePregnant at the time of cohort enrollment.Pregnant at any time during the cohort study.

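### Showing sex-specific effects only when the interaction p is below 0.05 defeats the plan's stated equity aim, and the 60-month age subgroup is empty or nearly so in Mali

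*SAP article*

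**What the plan says.** The section on subgroup analysis of the primary outcome tests each Table 8 variable through an arm-by-subgroup interaction, with the p-"value presented for the interaction term" in every case. Estimates by category are conditional: only if that p is below 0.05 does the plan state that "we will present separate effect estimates and confidence intervals for each category of the sub-group variable".

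Three rows of Table 8 matter here.

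- **Gender.** The rationale has two parts: possible effect modification through behaviour and occupation, and "to demonstrate equity of the intervention effect".
- **Age.** The categories are "≤ 60 months of age vs > 60 months of age", with no site restriction. The Eligibility section sets the Mali cohort at 5 years and older, "to exclude those covered by Seasonal Malaria Chemoprevention".
- **Season, marked Kenya only.** High season is the "four continuous months of the year with the highest clinical malaria incidence at local health facilities during the trial". Facility-recorded malaria is also a secondary outcome; of it the plan says "This outcome is assessed daily at routine health facilities and dispensaries (Mali and Kenya only").

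The Background section states that this is a master SAP and that site-specific SAPs may alter definitions and cutoffs.

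**The concern.** To show that an intervention works equally in boys and girls, one needs both estimates and their intervals, side by side, and needs them most when they agree. The reporting rule does the reverse: it shows the pair when they differ significantly and otherwise leaves only a p-value. A non-significant p can mean similar effects or too little information, and without the intervals a reader cannot tell which.

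The rule also distorts what is shown. When a real difference is modest, estimates appear only in those samples where the observed difference happens to be large.

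The age row raises a separate problem. A category that almost no Mali participant can enter yields no useful interaction test there. The season row raises a lesser one: the split is settled by malaria data collected after randomisation, on an outcome that the intervention is meant to lower.

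**Working it through.** The plan states no power or error rate for the subgroup analyses, so there is no figure of its own to reproduce. The following gives the scale.

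**1. How often equal effects are hidden.** With no interaction, p falls below 0.05 with probability 0.05. Estimates are withheld with probability 1 − 0.05 = 0.95.

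**2. What a non-significant p can rule out in Kenya.** Inputs from Table 2: 0.845 events per person-year in control, overall IRR 0.70, 1260 person-years in total (630 per arm). Assumptions of this review: an even sex split, Poisson counts, and a cluster effect that cancels because the sexes are compared within clusters.

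- Control events: 630 × 0.845 = 532. ATSB events: 532 × 0.70 = 373. By sex, about 266 and 186.
- SE of the log ratio of IRRs: √(2/266 + 2/186) = 0.135.
- For true IRRs of 0.6 and 0.8: ln(0.8/0.6) = 0.288; 0.288/0.135 = 2.13; power = Φ(2.13 − 1.96) ≈ 0.57.

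The plan gives other Kenya figures, and the same formula gives:

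| Source | Control events | SE | Power, 0.6 vs 0.8 |
|---|---|---|---|
| 1260 person-years (Table 2) | 532 | 0.135 | 57% |
| Stated enrolment: 70 × 13.5 × 2 years × 0.8 = 1512 person-years | 639 | 0.123 | 64% |
| 829 expected control events (interim analysis section) | 829 | 0.108 | 76% |

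A ratio of 0.75 pitted against 0.65 would be detected about 19% of the time on the first row. Under the same assumptions, 0.6 vs 0.8 is detected with 72% power in Mali at 0.40 per person-year (97% at 0.90, which is 0.6 events per 8 months annualised). In Zambia it is 74%, if 0.50 per 6-month season is read as 1.0 per person-year. Kenya is the least informative site, but power for a moderate difference is below 80% at all three unless Mali's higher rate applies.

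**3. Distortion of what is shown.** With SE 0.135, estimates appear only if the observed ratio of IRRs reaches exp(1.96 × 0.135) = 1.30 in either direction. A true ratio of 0.75/0.65 = 1.15 could be displayed only when its size is overstated or its direction reversed.

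**4. Mali age category.** Enrolment runs from 60 to 180 months. The lower category can hold only children of exactly 60 months: none if age is continuous. If age is kept in completed months and spread evenly (an assumption), the share is 1/120 = 0.8%. With 3850/2 = 1925 person-years per arm, that is 1925 × 0.40/120 = 6.4 control events and 6.4 × 0.70 = 4.5 ATSB events. At 0.90 per person-year it is 14.4 and 10.1.

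**5. Kenya season.** No arithmetic applies. As written, the split is one set of calendar months, applied alike to both arms, and the primary outcome comes from the cohort rather than from facility records.

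**The case against.** The strongest defence is that Table 8 is mainly about effect modification. For housing type, rainfall, baseline prevalence, and age in Kenya and Zambia, the interaction test answers the question asked, and its p-value is presented without condition. This stands. A reader might infer that none of the subgroup aims can be met, or that only significant subgroups will appear in the report; the text supports neither. Only the equity half of the gender rationale is defeated, together with age in Mali.

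A reader might also infer that subgroup data would be lost to later synthesis. The plan commits to a pooled individual-participant analysis and meta-analysis across the three trials, and datasets are available on reasonable request. At most, an outside synthesis that relies on published tables is affected.

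The chance of at least one spurious interaction, 1 − 0.95⁵ = 23% for five independent tests or 1 − 0.95⁶ = 26% for six, is not an argument for the change. It is a multiplicity figure and would be the same with all estimates shown.

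On Mali, the master SAP allows site documents to change cutoffs, so the Mali SAP, not shown here, may already repair this. That is fair. Still, the season row is marked for one country and the age row is not, so the master text as written applies the cut to Mali.

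On Kenya's season, a reader might infer bias. None is shown: the selection rule is stated in advance, the split is common to both arms, and a roughly proportional reduction need not move the peak months.

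**Conclusion.** The point holds in limited form. The p < 0.05 condition conflicts with the plan's own aim of demonstrating equity by sex: sex-specific IRRs would be withheld about 95% of the time when effects are equal. The p-value left in their place is weak evidence, with Kenya power for 0.6 against 0.8 of about 57% to 76%. Those powers rest on an even sex split, Poisson counts, and illustrative IRRs that are not in the plan. The 95% needs only a correctly sized test.

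The age subgroup cannot be informative in Mali as the master text stands, its lower category being empty or at most about 0.8% of the age range. The Kenya season definition is a minor matter of tidiness. The primary analysis is untouched, and this is a desirable correction to reporting rather than a serious flaw.

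**What to change.** - Replace the conditional sentence: report the IRR and 95% CI for every category of every Table 8 subgroup, with the interaction p alongside, whatever its value.
- Mark the 60-month age subgroup as Kenya and Zambia only, or give Mali a cut inside 5 to under 15 years. Table 7 lists a 60-month age split as a possible adjustment covariate and needs the same check for Mali.
- As a minor addition, fix Kenya's high-season months from pre-trial facility data.

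The cost is a few lines in the SAP and one forest plot per trial, with no new data on participants. The one small downside is that a season fixed from pre-trial data may fit the trial years less exactly.

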### Framework

The trials are planned under a superiority framework. The comparisons will consist of two-sided tests of the null hypothesis of no difference in efficacy between the ATSB (intervention) arm and the control arm. All primary comparisons will consist of comparisons of the outcome in the intervention arm vs. the outcome in the control arm.

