### Overwhelming benefit rule

The DSMBs of each trial may consider recommending an early submission of the ATSB dossier for overwhelming benefit if a test of the null hypothesis that the cumulative clinical incidence of malaria in the intervention arm in the intention to treat analysis population is lower than the cumulative clinical incidence in the intention to treat analysis population of the control arm. The null hypothesis was equal incidence between the two arms; the interim analysis assumes a two-sided test of the null hypothesis at a significance level of *α* < 0.001. This test will be conducted using a variance component regression model with a Poisson likelihood and a log link function which includes random cluster-level intercepts. The regression will include a fixed effect for study arm, and the hypothesis will be tested by testing that the incidence rate ratio associated with this covariate is not significantly different than 1 with a *p*-value < 0.001. The DSMB has been tasked with only making a recommendation about early referral of the trials to the vector control advisory group (VCAG) at the World Health Organization. This recommendation is only expected after the results of two trials show significant benefit, either in the interim or in the final analysis. As such the independent statistician working in collaboration with each trial site will advise the DSMB of each trial site on the results of the interim analysis as well as results of interim or final analyses of the other trials. The DSMB can thus include the interim results from other sites in their consideration of recommending an early referral to the VCAG.

A DSMB recommendation to discontinue the trial will not be based on the results of this statistical test. The DSMB can advise continuing the trial even if statistically the boundary is crossed, e.g., in order to continue collecting more epidemiological, entomological, or safety information or data for further sub-group analyses. It is the intent of the investigators to continue the trial even in the case of an early efficacy demonstration across more than one site since there is an expectation of significant heterogeneity in the effect of ATSB across entomological settings.

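### Table 8 tests effect modification by baseline prevalence and lagged rainfall only after a median or mean cut, which loses interaction power if the modification is a gradient

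*SAP article*

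**What the plan says.** Table 8 defines the baseline prevalence subgroup as "High vs. low (≥ median cluster prevalence vs. < median cluster prevalence" and the one-month lagged rainfall subgroup as "High vs. low (≥ mean for study site (country) vs. < mean for study site (country". The test of homogeneity is the "inclusion of the treatment, subgroup variable, and their interaction term as predictors in the adjusted models of primary outcome". The interaction p-value is always presented. If it "is less than 0.05, we will present separate effect estimates and confidence intervals for each category" of the subgroup variable; otherwise no subgroup estimates are promised.

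The stated reason for the prevalence subgroup is "Local endemicity may act as an effect modifier". For rainfall, the stated reason is that heavy absolute rainfall may blunt the effect by raising the mosquito carrying capacity. Table 8 gives a reason for each modifier but none for either cut-point.

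The uncut values exist. Table 7 (Covariate adjusted analysis) lists baseline prevalence as "Calculated at cluster level", without a cut. Total lagged rainfall must be held as a continuous quantity before it can be compared with its mean. The subgroup section also has missing values imputed before the variables are categorised.

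**The concern.** Both modifiers are continuous, and both cuts are sample statistics with no stated biological or programme meaning. Cutting a continuous modifier discards the variation within each half. If the ATSB effect changes steadily with endemicity or rainfall, the categorical test is weaker than one on the uncut variable.

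Two features of the plan raise the stakes. Baseline prevalence is a cluster-level modifier, and Table 2 gives only 70 to 76 clusters per trial, so interaction power is scarce to begin with. And the same test decides whether readers see subgroup estimates at all: a missed interaction leaves them with a p-value and no picture of how the effect varies.

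**Working it through.** **No stated figure to reproduce.** The plan gives no interaction effect size and no interaction power. The check therefore calibrates on the main effect and then compares the two codings under stated assumptions.

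**Inputs from Tables 2 and 3.** IRR 0.70; coefficient of variation k = 0.40; 38, 35 and 35 clusters per arm (Mali, Kenya, Zambia). Person-years per cluster: Zambia 1610/70 = 23; Kenya 1260/70 = 18; Mali 38 × 16/12 × 0.8 = 40.5. Alpha is 0.05, taken as two-sided because the Framework section specifies "two-sided tests of the null hypothesis of no difference in efficacy".

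**Calibration.** c = 1 + (z_α/2 + z_β)² × [(λ0 + λ1)/y + k²(λ0² + λ1²)] / (λ0 − λ1)².

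- Zambia, λ0 = 0.50, λ1 = 0.35, y = 23: [0.85/23 + 0.16 × 0.3725]/0.0225 = 4.29; c = 1 + 7.85 × 4.29 = 34.7; power at 35 per arm 80.4% (stated 80%). This takes 0.50 as a rate per person-year.
- Mali, λ0 = 0.40, y = 40.5: 87.6% (stated 88%).
- Kenya, λ0 = 0.845, y = 18: 84.0% (stated 80%). The gap does not bear on this point.

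**Closed form for the cut.** For a linear interaction, the categorical test has power Φ(ρ(z_0.975 + z_power) − z_0.975). Here ρ is the correlation of the modifier with its binary version, and z_power is the normal quantile of the continuous test's power. For a normal modifier cut at the median, ρ = √(2/π) = 0.798, so ρ² = 0.637. Example at 80%: 0.798 × (1.96 + 0.84) − 1.96 = 0.28, and Φ(0.28) ≈ 0.61.

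| Continuous test | After median split | Loss (points) |
|---|---|---|
| 20% | 14.3% | 5.7 |
| 30% | 20.8% | 9.2 |
| 40% | 27.5% | 12.5 |
| 50% | 34.6% | 15.4 |
| 70% | 50.9% | 19.1 |
| 80% | 60.8% | 19.2 |
| 90% | 73.4% | 16.6 |
| 95% | 82.0% | 13.0 |

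The loss passes 10 points at about 33% power.

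**Other shapes.**

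- Uniform, cut at the median (ρ = 0.866): loss 1.5 to 12.4 points.
- Clearly bimodal (ρ = 0.958): about 1 to 4 points.
- Right-skewed, cut at the mean (ρ = 0.735 to 0.762): about 18 to 20 points at 50% power and 23 to 26 at 80%.

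**Simulation for baseline prevalence.** Cluster log rates were regressed on arm, modifier and their interaction, with 2000 runs per setting. Rates per person-year were 0.845 (Kenya), 1.0 (Zambia, 0.50 per six-month season) and 0.6 (Mali, assumed). Assumed slopes are in log IRR per SD; 0.3 means an IRR of about 0.52 at −1 SD and 0.94 at +1 SD. With no modification and prevalence known exactly, both tests rejected in 4.7% to 5.8% of runs.

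| Loss in points at slope | 0.1 | 0.2 | 0.3 | 0.4 |
|---|---|---|---|---|
| Kenya, prevalence known exactly | 1.4 | 12.1 | 20.6 | 20.5 |
| Zambia, prevalence known exactly | 4.4 | 16.0 | 21.7 | 18.4 |
| Mali, prevalence known exactly | 5.2 | 14.0 | 19.3 | 14.6 |
| Kenya, Table 3 survey size | 1.0 | 6.8 | 15.9 | 20.2 |
| Zambia, Table 3 survey size | 1.8 | 8.0 | 17.9 | 21.1 |
| Mali, Table 3 survey size | 4.1 | 13.7 | 23.3 | 21.5 |

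The survey-size rows also let prevalence predict incidence at 0.2 per SD. A separate simulation (3000 runs, prevalence known exactly) used rates of 0.40, 0.845 and 0.50. At slope 0.3 it gave continuous against split power of 72% and 52% (Mali), 68% and 49% (Kenya), and 62% and 42% (Zambia).

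**Reverse case.** If the true modification is a step exactly at the median, the split wins. For a step of ±0.3 in Zambia, power is 66.6% with the split and 53.7% with the continuous term.

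**The case against.** These are secondary subgroup analyses, a high/low display is conventional, and a linear term imposes a shape of its own. The size of the loss rests on slopes and distributions that the plan does not give. The simulations use cluster log-rate regression rather than the planned adjusted Poisson mixed model, and they cover a fixed cluster-level modifier. Rainfall changes by month, so neither the simulation nor the argument from the number of clusters carries over to it; for rainfall there is only the closed form. All of this stands, and it limits the point to an inexpensive improvement. It does not supply a reason to prefer the cut.

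Four stronger readings are tempting, and the document does not support them.

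- A reader might infer that the cuts hide gradients the plan expects. Table 8 says only that the modifiers may act. The one stated expectation, "there is an expectation of significant heterogeneity in the effect of ATSB across entomological settings", is not tied to prevalence or rainfall within a site.
- A reader might take 10 to 20 points as this trial's loss. It is conditional on shape, slope and power.
- A reader might infer that site-specific medians prevent comparison across countries. The pooled analysis uses individual participant data, which can be recoded, and it will examine prevalence-related factors as modifiers without naming cuts.
- A reader might infer that a non-significant interaction will be reported as homogeneity. The plan does not say so.

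The Background allows site-specific SAPs to change cut-offs. A different cut-off is still a cut, and nothing there or in the pooled analysis supplies a continuous interaction test for the single trials.

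**Conclusion.** The point holds as a modest inefficiency in the subgroup analysis of each trial. The plan tests two continuous modifiers only through sample-based categories, and that test controls whether estimates are shown. For a roughly linear modification and a near-normal modifier, the median split gives up about 36% of the information on the interaction. That is about 10 to 20 points of power once the continuous test has roughly 33% or more, and less below that or for uniform or bimodal modifiers. A skewed modifier cut at its mean can lose more. All these figures rest on assumed interaction sizes and distributions. The primary comparison and its error rate are untouched.

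**What to change.** In the subgroup section and Table 8, for each trial:

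1. Make the homogeneity test for endemicity the interaction of arm with continuous cluster baseline prevalence, in the planned adjusted model.
2. Make the homogeneity test for rainfall the interaction of arm with continuous one-month lagged total rainfall, for example log-transformed. This should be the absolute rainfall of Table 8. The Table 7 anomaly is a different variable and would test a different hypothesis.
3. Report the IRR with its 95% CI at fixed values of each modifier, such as the 25th, 50th and 75th percentiles.
4. Keep the high/low split for descriptive display.

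The cost is a change of wording and one re-specified term per modifier, with no new data. It can be made when the site-specific SAPs are updated before data lock. The downside is some loss of power if the true modification is a step at the cut-point; the retained display would still show that pattern.
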